#### Comparisons of quality measures (worksheet vs. adherence checklists) and worksheet formats

If self-reported adherence (as assessed through the checklists embedded in clinical notes) is highly correlated with worksheets and/or the gold standard observer ratings, and if they are strongly associated with outcomes, the checklists alone may be deemed sufficient for quality assessment, because the notes can already be accessed by quality monitors in each system. First, we will use the Fisher *r*-to-*z* transformation to calculate a value of *z* that can be applied to assess the significance of the difference between two correlation coefficients. This analysis is conducted to assess whether a significant difference exists between correlations with the gold standard observer ratings. If there is no significant difference, this would indicate that the worksheet quality scoring strategy does not yield an advantage or disadvantage in terms of its correspondence with gold standard observer ratings. We will also use this strategy to determine whether a difference exists between correlations with worksheet formats (app vs. traditional paper form) and observer ratings [48].

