Researchers have also discovered limitations to existing indirect methods of monitoring fidelity, although they are sometimes used for pragmatic reasons [21]. Clinician self-reports of fidelity (e.g., checklists) appear to correspond only modestly with observer or client fidelity ratings [9, 12, 15, 24–26]. Both our preliminary work and published literature [27] indicate that clinicians (1) perceive adherence checklists as adding to an already high paperwork burden, (2) may not complete them as directed, and (3) may over- or underreport use of prescribed treatment elements. Literature on medical record review, checklists, and clinical progress notes to assess fidelity is mixed [28], and very little is specific to mental health [25, 28, 29]. One study indicated that record review may be a valid method of assessing clinician behavior [30], but research suggests that clinical progress notes convey poor estimates of frequency or intensity of EBPT techniques [30, 31]. Thus, conclusions about the interventions being delivered, and their quality, that can be drawn from self-report or clinical records may be limited.

While manualized CBTs exist for a wide variety of mental health conditions, a common element is the use of worksheets to teach and support client CBT skill development. Diagnosis-specific and transdiagnostic CBT protocols emphasize a set of core CBT elements, targeting clients’ behaviors and thoughts to reduce their symptoms. Both the behavioral and cognitive components of CBTs have been shown to impact symptom change for depression, anxiety, and PTSD [1, 32–35]. Worksheets are used in session to schedule specific behavioral activities and assess their impact on mood, anxiety, or sense of mastery. They are also used to guide one through the processes of cognitive restructuring, which helps clients learn to identify and challenge their maladaptive beliefs and generate balanced alternative thoughts [36, 37]. Assessing the quality of the worksheets that are completed with clinician guidance in sessions may therefore be a pragmatic and valid strategy to assess CBT quality. Thus, using worksheets completed in session to assess treatment fidelity may convey advantages over time-intensive observer ratings and imprecise self-reports of session content.

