#### Convergent validity

Observer-rated competence on full sessions were not significantly correlated with worksheet ratings (*r*_*pb*_ = .278, *p* = .068), but we found high (Spearman rank) correlations between our worksheet rating method and observer ratings for worksheet-related CBT elements (e.g., cognitive restructuring, *r*_*pb*_ = .823; *p* = .000). Similarly, correlation between observer-rated adherence (*n* = 44 sessions) and adherence scores based on worksheets was low for full sessions (*r*_*pb*_ = .062, *p* = .68) but high for worksheet-related items (*r*_*pb*_ = .808; *p* = .000).

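### The checklist can be accepted as sufficient for quality assessment on agreement with the worksheet score plus outcome association, with no required agreement with the gold standard observer ratings

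*Protocol article*

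**What the plan says.** The rule is in the Protocol article, section Comparisons of quality measures (worksheet vs. adherence checklists) and worksheet formats. It applies if self-reported adherence "is highly correlated with worksheets and/or the gold standard observer ratings, and if they are strongly associated with outcomes". It has two parts.

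- **Agreement:** a high correlation with the worksheets, with the observer ratings, or with both.
- **Outcome:** "and if they are strongly associated with outcomes, the checklists alone may be deemed sufficient for quality assessment".

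The same section then plans a Fisher r-to-z test: "This analysis is conducted to assess whether a significant difference exists between correlations with the gold standard observer ratings". A non-significant result is taken to mean that "the worksheet quality scoring strategy does not yield an advantage or disadvantage in terms of its correspondence with gold standard observer ratings". The Concurrent validity section plans Spearman correlations of the worksheet method with observer ratings for the overall measure, each subscale and the conceptually corresponding items. Neither analysis is written as a condition for accepting the checklist.

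Three other sections bear on the rule.

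- Convergent validity (pilot): "Observer-rated competence on full sessions were not significantly correlated with worksheet ratings" (r = .278, p = .068). For full-session adherence the correlation was .062 (p = .68, 44 sessions). For worksheet-related elements the correlations were .823 and .808.
- Background: clinician self-reports of fidelity "appear to correspond only modestly with observer or client fidelity ratings".
- CBT fidelity: observers will rate 10% of the session recordings.

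**The concern.** The study has one criterion for fidelity, the observer rating, and two cheaper candidates, the worksheet score and the checklist. The and/or allows one candidate to serve as the reference for the other before it has been validated. If the checklist agrees with the worksheet but not with the observers, the agreement part is still met.

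This case is foreseeable. The Background already reports only modest correspondence between self-report and observers, and the pilot found weak correspondence between worksheets and full-session observer ratings. A checklist scored as the proportion of elements ticked (Raters and scoring) could then be recommended for quality monitoring although it does not reflect observed fidelity. The study was set up partly because of that limitation of self-report.

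**Working it through.** **Inputs.** Worksheet-observer correlation *a*, from Convergent validity: .278 and .062 (full session), .823 and .808 (worksheet-related items). Pilot n = 44, stated for adherence and assumed here for competence. The article puts no figure on a high correlation, so the checklist-worksheet correlation *b* is assumed to be .70, with .80 as an alternative.

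**1. Pilot figures.** t = r·√((n − 2)/(1 − r²)), 42 degrees of freedom, two-sided.

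- r = .278: t = .278 × √(42/.9227) = 1.88, p = .068. The article gives .068.
- r = .062: t = .062 × √(42/.9962) = 0.40, p = .69. The article gives .68, a difference of no consequence.

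**2. What worksheet agreement implies about observer agreement.** If checklist and observer rating are unrelated given the worksheet, their correlation is the product *ab*. Without that assumption it can lie anywhere in *ab* ± √((1 − a²)(1 − b²)). With *b* = .70:

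| Worksheet-observer *a* | Product *ab* | Possible range |
|---|---|---|
| .062 (full-session adherence) | .04 | −.67 to .76 |
| .278 (full-session competence) | .19 | −.49 to .88 |
| .808 (worksheet-related, adherence) | .57 | .15 to .99 |
| .823 (worksheet-related, competence) | .58 | .17 to .98 |

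For *a* = .278: .70 × .278 = .195 and √(.9227 × .51) = .686, so .195 − .686 = −.49 and .195 + .686 = .88.

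The ends of each range need a partial correlation of −1 or +1 and are not forecasts. Zero is less remote. At *a* = .278 it needs a partial correlation of −.195/.686 = −.28. Zero is possible whenever a² + b² ≤ 1, that is, for *a* up to .71 when *b* = .70, or up to .60 when *b* = .80.

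**3. Does the outcome condition close the gap?** Assume *b* = .80, worksheet-outcome r = .30 and observer-outcome r between 0 and .30, and require a valid four-variable correlation matrix. At *a* = .278 the range without the outcome condition is −.35 to .80. With checklist-outcome r = .30 it is −.35 to .79, and with .50 it is −.31 to .78. Zero remains possible.

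**4. Does the Fisher test close the gap?** It compares the two correlations with each other and does not require either to be high, so two equally poor measures would show no difference. Its power is also uncertain. If 360 clients × 6 sessions × 10% = 216 sessions are rated, separating .278 from .10 gives z = (.2855 − .1003)/√(2/213) = 1.91, and power is 48%. Dividing 216 by the stated design effect of 2.04 leaves about 106 sessions and power of 26%. With 16 sessions per client (576 rated) the figures are 88% and 59%. These are approximations. Both correlations come from the same sessions but are treated as independent, and the design effect was stated for the outcome analysis, so using it here is illustrative.

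**The case against.** The strongest reply is that outcome association is mandatory and is the study's leading validity criterion. The data collection summary names association with subsequent symptom change as the primary outcome, and the sample size section powers the study for predictive validity. A reader might infer that the checklist can qualify by agreeing with the worksheet score alone. The documents do not support that, because the second condition is joined by a plain and.

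The Background also gives a reason not to make full-session observer scores an absolute gate. It calls their link with outcome unclear, cites a meta-analysis with no overall link, and asks for attention to critical treatment elements. This stands, and the fix allows for it. It also cuts the other way: if fidelity and outcome can come apart, outcome association cannot stand in for observed fidelity.

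A reader might further infer that the worksheet says nothing about the gold standard. The pilot values of .823 and .808 contradict that for worksheet-related items, where the lower limits in the table are positive. Nor do the documents support the inference that observer agreement goes unexamined: the correlations are planned and will be visible. The wording is also permissive, in a condensed article. What remains is that visibility is not a requirement, and this is the only sufficiency rule for checklists that the article states.

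**Conclusion.** The point holds in a limited form. As written, the checklist may be accepted as sufficient for quality assessment on high agreement with the worksheet score and a strong association with outcomes, without any required agreement with the gold standard observer ratings. Neither the Fisher test nor the concurrent-validity correlations gate that conclusion.

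The size depends on which observer score applies. At an assumed checklist-worksheet correlation of .70, with checklist and observer unrelated given the worksheet, the implied checklist-observer correlation is .04 to .19 on the full-session pilot values and .57 to .58 on the worksheet-related items. Zero or negative values are possible in the first case and not in the second. The assumed .70 and .80, and the outcome correlations in step 3, are not from the article. The pilot correlations are, and they rest on few sessions.

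**What to change.** Delete the words that offer the worksheets as an alternative reference. Sufficiency as a quality (fidelity) measure would then require both a high correlation with the observer ratings and a strong association with outcomes. State in advance whether the observer criterion is the total score or the conceptually corresponding items already named under Concurrent validity.

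Report the checklist-worksheet correlation descriptively. Add that, if only worksheet agreement and outcome association are found, the conclusion is limited to the checklist being a comparable predictor of outcome and does not extend to its being sufficient to assess fidelity.

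This is a change of wording to a stated decision rule. The observer ratings are already planned, so no new data are needed. The cost is that the checklist loses the easier route to qualification and depends on the 10% of recordings with observer ratings.

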#### Client inclusion criteria

Eligible clients (*n* = 360) will be (1) adult outpatients (ages 18 or older), with a clinician diagnosis of primary PTSD (PTSD-Checklist-5 score of 33 or above) [48], a depressive disorder (e.g., major depressive disorder, dysthymia; Patient Health Questionnaire score of 10 or above) [49], or an anxiety disorder (Beck Anxiety Inventory score 22 or above) [50, 51]; (2) those who are willing to allow the team to collect session recordings, measures, notes, and worksheets; (3) those who are able to read and write at a 6th-grade level or above; and (4) those who are willing to engage in CBT.

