### Procedure

#### Recruitment and informed consent

Clinicians will be recruited through previously used recruitment strategies including presentation at clinical team meetings (at participating clinics), at CBT trainings, and/or by email. Private practitioners will be targeted through emails to professional organization listservs. After the informed consent, they will complete the clinician measures. They will be provided with an iPod touch, if needed, to use the mobile app. Their clients will be recruited using strategies approved by local systems and IRBs, such as waiting room flyers, whiteboard videos, and/or clinician or intake coordinator referral. Informed consent will be completed by study staff. Clients will then be randomized into one of two worksheet completion strategies: mobile app vs. paper form. Their sessions will be audio-recorded, worksheets will be collected, and they will complete symptom measures (every session for primary problem, every fourth for additional measures) for up to 16 sessions.

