#### CBT fidelity

We will use the Cognitive Therapy Rating Scale (CTRS) [60, 61], the “gold standard” observer rating scales for CBT for all sessions, and for CPT sessions, we will also use the CPT observer rating scale [21]. Trained postdoctoral fellows and advanced graduate students will rate 10% of the session recordings. They will overlap on 10–15% of these sessions to facilitate reliability analyses. ICCs for observer ratings in our previous studies using these instruments have been high, ranging from .79 to .84 ([45]; Monson et al.: A randomized controlled trial of training and consultation methods to deliver cognitive processing therapy for posttraumatic stress disorder: Impact on patient outcomes, submitted).

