#### Sample size justification and power calculations

In light of the project’s emphasis on the development of pragmatic measurement strategies that predict changes in the target problems, we powered the study to test for predictive validity. Calculations of a design effect (measure of how the design effects the standard error of the parameters) [81, 82] accounted for clustering. We computed ICC with repeated observations of clients at the clinic (*r*_*pb*_ = .01), clinician (*r*_*pb*_ = .01), and client (*r*_*pb*_ = .10) level in our prior research, assuming three clients per clinician, and six clinicians per cluster, and six observations per client, yielding a design effect of up to 2.04. We based the estimated number of observations per client to conservatively account for potential 37% client-level attrition and missing data during the treatment. For the growth curve analyses to assess whether the quality measure predicts symptom change (our primary analysis), the probability of a type 1 error (alpha) at two-tailed .05 power exceeds .80 for an effect size of *r* = .30, which corresponds with small-to-medium effects of fidelity on symptoms in prior CBT fidelity research [68, 83]. We also projected a sample size to be sufficient to conduct separate analyses and test for interactions with disorder (PTSD vs. depression vs. anxiety), app vs. paper form, and other variables of interest, and detect an effect size of .50, a medium effect.

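### A non-significant Fisher test is read as no advantage or disadvantage, in an observer-rated 10% subset that leaves moderate differences open and, for app vs paper, wider ones

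*Protocol article*

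**What the plan says.** The rule is in the protocol article, section on comparisons of quality measures and worksheet formats. A Fisher r-to-z test is used "to assess whether a significant difference exists between correlations with the gold standard observer ratings", that is, worksheet score against observer rating versus checklist score against observer rating. The reading of a negative result is then fixed: "If there is no significant difference, this would indicate that the worksheet quality scoring strategy does not yield an advantage or disadvantage", with the limiting clause that this concerns correspondence with the observer ratings. The section continues: "We will also use this strategy to determine whether a difference exists between correlations with worksheet formats" (app, paper) and the observer ratings. It also says that, under stated conditions, "the checklists alone may be deemed sufficient for quality assessment".

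Three other sections bear on this:

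- **CBT fidelity:** the raters "will rate 10% of the session recordings".
- **Concurrent validity:** worksheet ratings are predicted to be more accurate than the checklists.
- **Sample size justification:** the study is powered for predictive validity (r = .30, two-tailed alpha .05, power above .80). The sample is also projected to suffice for separate analyses and interactions, app vs paper among them, at an effect size of .50.

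No margin, interval or precision target is attached to the Fisher comparison.

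**The concern.** A non-significant test means the data are compatible with no difference. It does not mean they are incompatible with a difference that matters. Under the rule as written, fewer rated sessions or noisier ratings make a conclusion of no advantage or disadvantage more likely, so imprecision is rewarded. The plan predicts that worksheets will do better than checklists, and a failure to confirm that prediction would be reported as a finding of no difference.

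This is a defect in a sentence the article does state. It is not a detail left to a fuller plan, since a plan that followed the sentence would carry the error forward. At stake are two of the article's listed questions: whether the worksheet measure performs better than the checklist, and whether the formats differ in concurrent validity.

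**Working it through.** **The plan's own figure.** Power for one correlation is Φ(atanh(r)·√(n − 3) − 1.96). With r = .30 (atanh = .3095) and n = 360/2.04 = 176.5, this is Φ(4.08 − 1.96) = .98. Removing 37% of clients as well (226.8/2.04 = 111.2) gives .90. The stated power above .80 for the primary analysis is reproduced. No figure for the Fisher comparison exists to reproduce.

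**Rated sessions (assumed range).** There are 360 clients (client inclusion criteria). The planning value is six observations each ("assuming three clients per clinician, and six clinicians per cluster, and six observations per client"), and collection runs "for up to 16 sessions".

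- Lower: 360 × 6 × 10% = 216
- Upper, with no loss: 360 × 16 × 10% = 576
- Per format arm, assuming 1:1 allocation (the ratio is not stated): 108 to 288

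**Formula.** On the z scale, SE = √(1/(n₁ − 3) + 1/(n₂ − 3)). The 95% half-width is 1.96·SE, and the difference detectable with 80% power is 2.80·SE. This is the independent-correlation form without clustering.

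| Comparison | n per correlation | SE | Half-width (z) | Detectable difference (z) |
|---|---|---|---|---|
| Worksheet vs checklist | 216 | .097 | .19 | .27 |
| Worksheet vs checklist | 576 | .059 | .12 | .17 |
| App vs paper | 108 | .138 | .27 | .39 |
| App vs paper | 288 | .084 | .16 | .24 |

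**Worksheet vs checklist at 216.**

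- With an observed difference of zero, the interval around r = .50 reaches down to about .34.
- The difference detectable with 80% power is .50 vs .27. Gaps of about .15 to .25 in r therefore stay open.
- Power is .87 for a z difference of .30 and above .99 for .50.
- If the result is only just non-significant, the interval extends to twice the half-width, about .50 vs .17.

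**App vs paper at 108 per arm.** The observed app correlations that would be non-significant depend on the paper correlation, which the plan does not give:

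- Paper r = .278 (the preliminary full-session competence value): about .01 to .50
- Paper r = .50 (assumed): atanh = .549, and .549 ± .271 gives .27 to .67
- Paper r = .81 (near the preliminary worksheet-related items, .808 and .823): .69 to .89

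Power for .50 vs .30 is Φ(.240/.138 − 1.96) = .41. With 288 per arm, power for .50 vs .40 is Φ(.126/.084 − 1.96) = .32.

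**Dependence.** Worksheet and checklist correlations share sessions and observer rating. A dependent-correlation variance at 216 sessions, with both r = .50 and an assumed correlation of .2 to .5 between the two measures, gives a half-width of .18 to .15.

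**Clustering.** Dividing by the plan's upper design effect of 2.04 gives 106 sessions (half-width .27; power .95 for a z difference of .50) and 53 per format arm (half-width .39). That is probably too severe for a 10% sample. If sessions are drawn at random, a rated session has on average .5 other rated sessions from the same client (5 × 10%), 1.7 from the same clinician (17 × 10%) and 10.7 from the same cluster (107 × 10%). With the stated ICCs the design effect is 1 + .10 × .5 + .01 × 1.7 + .01 × 10.7 = 1.17, or about 184 effective sessions and a half-width of .21. How strongly the fidelity ratings themselves cluster is not given.

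**The case against.** Several points on the other side stand.

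- **Strength of the claim.** The article says would indicate, not proves, and confines the statement to correspondence with observer ratings.
- **Large differences.** A reader might infer that the 10% subset cannot exclude large differences at all. For worksheet vs checklist the figures do not support that. At 216 sessions a z difference of .50 would almost always be detected, even after the full design effect (.95), and a dependent-correlation test is sharper still.
- **Checklist-only recommendation.** A reader might infer that a small subset alone could lead to checklists being adopted. The article also requires a high correlation with worksheets and/or observer ratings and a strong association with outcomes. Even then it says only that checklists may suffice.
- **Interchangeable formats.** The no-advantage sentence names the worksheet scoring strategy. For app vs paper the article reuses the test, and reuse of the interpretation is implied, not stated. Formats are also compared on outcome associations and stakeholder views.
- **Sample size.** The .50 projection names app vs paper, so it is not true that only predictive validity was considered. It is not stated for a difference between correlations, however.
- **Choice of r.** The wide app vs paper range depends on the assumed correlation and narrows considerably near .81.

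None of this rescues the sentence. Without a margin, non-rejection does not establish similarity at any sample size. The remark in the Analyses section about associations that differ only slightly concerns outcomes and sets no margin for agreement with observer ratings.

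**Conclusion.** The concern holds in limited form: the sentence draws an invalid inference and should be changed.

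For worksheet vs checklist, the half-width is about .19 to .12 on the z scale for 216 to 576 rated sessions. At the lower end moderate differences remain open and very large ones do not, unless the result is only just non-significant. For app vs paper, the half-width is .27 to .16 for 108 to 288 per arm, so a non-significant result is weak evidence of similarity unless the correlations are high.

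These figures assume the 216 to 576 range, 1:1 allocation, the independent-correlation formula and no clustering. Clustering widens them, and allowing for dependence narrows the worksheet vs checklist figures. The comparison is secondary. The primary analysis of quality against symptom change is unaffected.

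**What to change.** Replace the sentence on non-significance with a rule of this kind:

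1. Report each difference in correlations with observer ratings with a 95% CI that allows for clustering by clinician. For worksheet vs checklist, use a dependent-correlation method, because both share the same sessions and observer rating.
2. Conclude no meaningful advantage or disadvantage only if the whole CI lies inside a margin fixed before the comparison is analysed. The margin is the largest difference in correlation the team would be willing to ignore.
3. Otherwise report the comparison as inconclusive.
4. State that the same rule applies to app vs paper.

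The cost is a wording change and one agreed margin, with no new data. The downside is that some comparisons, notably app vs paper, may be reported as inconclusive. A margin narrower than the half-width cannot be met: under the assumptions above, below about .27 on the z scale with 108 sessions per arm, or about .19 for worksheet vs checklist at 216 by the independent-correlation formula.

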#### Concurrent validity

We will compare our strategy to the “gold standard” fidelity measure and clinical progress notes alone. We predict that ratings on our quality monitoring method will be highly correlated with existing [3, 17] objective and reliable observer ratings and that they will be more accurate than the ratings based on the checklists embedded in the clinical notes alone [2, 21, 70, 71]. We will examine Spearman rank correlations [72] between our method and independent observer ratings for the overall measure, for each subscale and for conceptually corresponding items. Further, we will conduct cross-validation borrowing the idea of checking internal validity of prediction models in statistical learning [73].

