#### Analyses

We will first examine distribution of key variables for skewness, variability, and outliers and apply appropriate transformation or other strategies to address non-normality (e.g., robust estimation procedures) as necessary. Symptom scores from instruments that reflect the target problem for each client (e.g., depression, anxiety, or PTSD) will be standardized, and the standard scores will be used as the dependent variable (DV). We will also conduct secondary analyses with the measures for each target problem and with the functioning measure as DVs. The study will produce hierarchical data with repeated measures (Level-1) nested within clients (Level-2) nested within clinicians (Level-3). To evaluate change in client outcomes, we will conducted multilevel regression (i.e., mixed-effects regression, hierarchical linear modeling) growth curve analysis, which offers numerous strengths for analyzing change in nested data, including efficiency in handling missing data, powerful and accurate estimation procedures adjusting for clustering, and modeling flexibility (e.g., allows for the inclusion of continuous or categorical, time-invariant or time-varying covariates and predictors). We will employ strategies to check the sensitivity of analysis results due to missing data (e.g., pattern mixture modeling) [76]. We will analyze the intent-to-treat sample [77] and completer samples. First, multiple unconditional change models (i.e., change without predictors) will be evaluated to determine the most reliable and powerful way to analyze change (e.g., linear or non-linear change; modeling time as time since baseline or as session number) and determine the most appropriate variance-covariance structure, considering, among others, the autoregressive structure.

The first set of multilevel regression analyses will evaluate trajectories of outcomes over the entire course of therapy or over the course of several sessions. We will examine the influence of potentially significant covariates (e.g., baseline scores, setting, veteran status, client skill, and other clinician, setting, or client characteristics) and include in exploratory analyses. Given the small number of systems, the system will be entered as a potential covariate to assess and adjust for its influence, but we will conduct an exploratory analysis with the system entered at Level-4.

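### The app-versus-paper comparison uses the Fisher r-to-z test on what appear to be Spearman correlations from nested sessions, so its standard error can be too small: mildly to moderately when the correlation is high, little when it is low and clustering is weak

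*Protocol article*

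**What the plan says.** The section on comparisons of quality measures and worksheet formats adopts the Fisher r-to-z transformation, giving a z that "can be applied to assess the significance of the difference between two correlation coefficients". It is introduced for worksheets against checklists and then extended to format: "We will also use this strategy to determine whether a difference exists between correlations with worksheet formats (app vs. traditional paper form) and observer ratings". The section names no type of correlation, variance formula, unit of analysis or significance level.

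The type of correlation appears under Concurrent validity: "We will examine Spearman rank correlations [72] between our method and independent observer ratings for the overall measure, for each subscale". The pilot also reports rank correlations: "we found high (Spearman rank) correlations between our worksheet rating method and observer ratings for worksheet-related CBT elements". The Analyses section describes the data as "hierarchical data with repeated measures (Level-1) nested within clients (Level-2) nested within clinicians (Level-3" and uses multilevel models for client outcomes. It does not extend them to the correlation comparisons. Format is allocated by client: "Clients will then be randomized into one of two worksheet completion strategies: mobile app vs. paper form". A clinician can therefore have clients in both formats.

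**The concern.** Two features of the data depart from what the Fisher test assumes. The transformed Spearman coefficient has a larger variance than the transformed Pearson coefficient, and the gap grows with the correlation. Sessions from the same client or clinician are also not independent pairs. In the settings checked below, both made the computed standard error too small, so differences are declared too often.

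Whether app and paper differ in concurrent validity is the fifth question listed in the data collection and research strategy summary. The Discussion presents validation across platforms as information for implementation. A spurious advantage for one format could influence that choice.

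**Working it through.** **Inputs from the article**
- 120 clinicians and 360 clients, so 360/120 = 3 clients per clinician. Up to 16 sessions per client; the power section assumes 6 observations.
- 10% of session recordings get an observer rating (CBT fidelity).
- Pilot correlations (Convergent validity): .823 and .808 for worksheet-related items; .278 and .062 for full sessions.
- ICCs of .01 (clinic), .01 (clinician) and .10 (client), given in the power section for the symptom-change analysis. None is given for fidelity or worksheet ratings.

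**Assumptions**
- Nominal two-sided .05. The article states that level only for the primary growth-curve analysis, so there is no figure of its own to reproduce here.
- 1:1 allocation to format.
- Any clustering of fidelity ratings stronger than the ICCs above.

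**Step 1: rated sample.** With 6 sessions per client, 360 × 6 × .10 = 216 rated sessions. With 16 sessions, 360 × 16 × .10 = 576. That is 108 to 288 per format, 0.6 to 1.6 per client and 1.8 to 4.8 per clinician.

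**Step 2: baseline.** On independent Pearson pairs the Fisher test kept its level in simulation (.045 to .054). The test is sound for the data it was made for.

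**Step 3: rank effect alone.** The Bonett-Wright variance for Spearman is (1 + r²/2)/(n-3). With V = 1 + r²/2, the true error is 2[1 − Φ(1.96/√V)].
- r = .823: V = 1.339, 1.96/√V = 1.694, error .090
- r = .808: V = 1.326, 1.96/√V = 1.702, error .089
- r = .5: V = 1.125, error .065
- r = .278: V = 1.039, error .054
- r = .062: V = 1.002, error .050

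This formula is an approximation. Simulation at r = .8 without clustering gave .070 to .083. Fieller's constant of 1.06 would give only .057, below the simulated values.

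**Step 4: adding clustering.** Simulated rejection rates of the Fisher test on Spearman coefficients, with no true difference, 120 × 3 clients, 10% of sessions rated, 6 to 16 sessions per client and 3,000 to 4,000 runs. The Monte Carlo standard error is about .005 at a rate of .07: √(.07 × .93/3,000).

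| Clustering of ratings | r about .8 | r about .3 | r about .06 |
|---|---|---|---|
| None | .070–.083 | .051–.052 | .045–.049 |
| Clinician .01, client .10 (the article's ICCs) | .069–.079 | .052–.059 | .047–.050 |
| Clinician .3, client .2 (assumed) | .087–.109 | .066–.095 | .060–.087 |
| Clinician .5, client .2 (assumed) | .106–.165 | .083–.132 | .077–.134 |

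A second simulation assumed variance shares of .4 (clinician) and .2 (client), with 0 to 50% of each measure's error stable within client. At a Spearman correlation of about .81 it gave .084–.094 with 6 sessions, .098–.117 with 10 and .097–.136 with 16. A repeat gave .085–.138 overall.

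At the article's ICCs clustering adds almost nothing, because the inflation for a correlation follows roughly the product of the two measures' ICCs.

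**Step 5: correcting only for ranks.** Using (1 + r²/2)/(n-3) brought the error to .038–.048 at the article's ICCs. Under the strong assumed clustering it still reached about .086.

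**The case against.** The strongest reply is that the defect is partly inferred and often small. The comparison section does not name Spearman; that comes from Concurrent validity. The standard-error formula and the handling of repeat sessions are details that an article may leave to a fuller document. If the overall measure behaves as the pilot's full-session ratings did (.278 and .062), the rank effect is negligible. The comparison is secondary, the primary model handles nesting, and no stated decision rule turns on this p-value.

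Most of this stands and limits the size of the point. It does not remove it. The article names a test, and the only coefficient it names for this relation is one that the test's usual variance does not fit. It also predicts high correlations and will examine conceptually corresponding items, where the pilot found about .8.

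Three stronger readings are tempting, and the article does not support them.
- **The test errs about twice as often as stated.** No error rate is stated for this comparison. A true rate of .10 needs a variance ratio of (1.96/1.645)² = 1.42. The article's figures do not give that, and it is reached only with assumed clustering.
- **The design effect of 2.04 implies an error of .17.** That value does follow from 2[1 − Φ(1.96/√2.04)]. But the design effect was computed for the symptom-change analysis with six observations per client, and does not carry over to a correlation on a 10% sample.
- **The two correlations come from the same sessions.** That would apply to worksheets against checklists. App and paper have different clients, so the independent-groups form is reasonable at client level. The dependence that remains comes from repeat sessions and shared clinicians.

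**Conclusion.** The concern holds as a calibration problem of modest, conditional size. At a nominal two-sided .05, the false-positive rate for app against paper is:
- about .07 to .09 at correlations near .8, from the rank effect alone or with the article's ICCs;
- about .09 to .14 at such correlations if fidelity ratings cluster strongly within clinician and client (up to .165 in the most extreme setting tried);
- close to .05 at correlations of .06 to .28, unless clustering is strong.

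The first range assumes that the compared coefficients are Spearman and that 1/(n-3) is used at session level. The second also rests on clustering values that the article does not supply. Recruiting clinicians with varying CBT expertise makes clinician clustering of fidelity plausible, but does not establish it.

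**What to change.** In the section on comparisons of quality measures and worksheet formats, replace the Fisher test for app against paper with this: the difference between the two Spearman coefficients, with a 95% confidence interval from a bootstrap that resamples clinicians together with all their clients and sessions. This allows for ranks, repeat sessions and clinicians shared between formats in one step. Its error rate was not simulated here; the recommendation rests on its matching the structure of the data.

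Substituting (1 + r²/2)/(n-3) for 1/(n-3) is a partial measure. It corrects the rank effect but not the clustering.

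The change costs one sentence and a few lines of code, and needs no new data. The downside is a somewhat wider interval for a secondary comparison.
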